### Patient and public involvement

Participant burden of the intervention and outcome measures were assessed using individual interviews and informal feedback from patients participating in two pilot studies.^27 33^ Patients will not be involved in recruitment of participants or conduct of the study. Results of this study will be disseminated to participants through presentation at client and community forums.

### Study design and setting

The study is a double-blind RCT with four arms exploring the efficacy of online ABM training versus a placebo training condition theorised to offer no specific therapeutic benefits. The choice of comparator was selected as placebo training closely mimics ABM training, and is frequently used as a comparator in ABM studies (eg, refs 25 26 34 35). The study will take place in a location of the participant’s choice (which we anticipate will typically be their home) and will be accessed via personal computer connected to the internet.

The study design has a 2×2×3 experimental structure, with multiple non-commensurate dependent variables measuring pain intensity and interference, emotional functioning, and pain-related disability. Treatment is a two-level factor (ABM, placebo), and the number of sessions is a two-level factor (10 sessions, 18 sessions), with measures recorded at three points in time (baseline, endline and 6-month follow-up). Measures in the 18-session groups (18AMG and 18PTG) will also be taken after session 10.

### Randomisation and sample size

Block randomisation of size four, performed via a randomisation command in the LifeGuide platform,^36^ will be used to sequentially randomise eligible consecutive consenting participants to one of four groups: (1) 10-session attentional modification group (10AMG); (2) 10-session placebo training group (10PTG); (3) 18-session attentional modification group (18AMG); or (4) 18-session placebo training group (18PTG). This blocked randomisation will be performed separately for those aged 16–24 and those aged 25–60. An allocation concealment mechanism will be used to ensure neither participants nor researchers know the study group to which the next participant will be assigned. This will be automatically performed within the LifeGuide platform (see The intervention section), with participants provided access to appropriate AMG or PTG sessions. Participants randomised to either 10-session condition will receive ten 35 min online sessions across a 4-week period, while those randomised to either 18-session condition will receive eighteen 35 min online sessions across an 8-week period. All online sessions will be administered twice a week on a separate set of days (Monday–Thursday, Tuesday–Friday). Participants randomised to either AMG condition will receive attentional training via the modified training version of the probe-classification visual-probe task, while those randomised to either PTG condition will receive placebo training via the standard version of the probe-classification visual-probe task. To maintain the overall quality and legitimacy of the intervention, code breaks (ie, unblinding) will only occur in exceptional circumstances. Adherence will be monitored electronically via LifeGuide.

Our previous lab-based, proof-of-concept ABM intervention found reductions in pain intensity and pain interference from pre-ABM to post-ABM were associated with large effect sizes,^27^ although differences in methodology including delivery (online vs lab-based) and number of sessions warrant a more conservative estimate. On this basis, the study will recruit a minimum of 100 with 1:1:1:1 randomisation. This study is powered primarily to establish treatment efficacy for the primary outcome variable of pain interference by considering baseline and measures after session 10 between those randomised to an attentional modification arm and those randomised to a placebo arm. Randomisation should ensure baseline comparability on measures between these two groups, and a difference in beneficial outcomes between these groups will be modelled using a linear mixed model. For an assumed correlation of 0.7 between baseline and end of session 10 measures, a total of 40 per group (ie, 20 per randomised arm) would be needed to detect small to moderate standardised intervention differences (Cohen’s *d*=0.25) with at least 80% power (alpha=0.05, two-sided). The recruitment strategy includes a 20% oversampling to mitigate a loss of power from loss to follow-up.

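### With 40 per pooled group and a correlation of 0.7, power for d=0.25 is about 30% to 34%, not 80%; the trial reaches 80% power near 0.45 to 0.49 SD

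*Protocol article*

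**What the plan says.** The sample size argument is in the protocol article, Methods and analysis, Randomisation and sample size. The trial is powered on pain interference, using baseline and the measure after session 10, for the contrast "between those randomised to an attentional modification arm and those randomised to a placebo arm". The two attentional modification arms are thus pooled against the two placebo arms, and a linear mixed model is named for the comparison.

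The inputs are all given. "For an assumed correlation of 0.7 between baseline and end of session 10 measures", the section states that "a total of 40 per group (ie, 20 per randomised arm) would be needed to detect small to moderate standardised intervention differences" and gives the value as Cohen's "d*=0.25) with at least 80% power (alpha=0.05, two-sided"). Recruitment follows from that: "the study will recruit a minimum of 100 with 1:1:1:1 randomisation", and "The recruitment strategy includes a 20% oversampling to mitigate a loss of power from loss to follow-up".

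The Quantitative analyses section specifies random intercepts with treatment, number of sessions and assessment stage as fixed factors. The primary analysis has two stages, and baseline is one of them.

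**The concern.** A two-group comparison at d=0.25 with no baseline information needs about 252 per group for 80% power (normal approximation). A correlation of 0.7 reduces that number, but not to 40. The section describes 0.25 as a standardised intervention difference and gives no other definition, so it has to be read as a difference between treatment groups in SD units of the outcome.

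If the figure is wrong, the protocol promises a sensitivity that the trial does not have. The section also argues that a more conservative effect than the large pre-to-post effects of the earlier laboratory study is warranted, and 0.25 expresses that caution. A reader who relies on the power statement could take a non-significant result as evidence against a small to moderate effect, although the trial would miss such an effect about two times in three.

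**Working it through.** **Inputs**, all from Randomisation and sample size: n = 40 per pooled group (80 in total), r = 0.7, two-sided alpha 0.05, d = 0.25. The effect is standardised, so the outcome SD is set to 1.

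**1. Reproducing the stated figure.** Two calculations come out at about 80 participants. Neither tests a between-group difference of 0.25 SD.

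- *Repeated-measures interaction with f = d/2 = 0.125.* The noncentrality is f² × N × 2/(1 − r). At N = 80 this is 0.015625 × 80 × 2/0.3 = 8.33, which gives power 81.4%. The smallest adequate N is 78 (80.4%). In a 2×2 interaction each cell departs by one quarter of the difference in change, so f = 0.125 is a difference of 4 × 0.125 = 0.50 SD. The change-score test at 0.50 SD has the same noncentrality, 0.50²/(0.6 × 2/40) = 8.33, and the same 81.4%. The f that matches d = 0.25 is 0.25/4 = 0.0625. It gives power 29.7% at N = 80 and requires N = 304.
- *Paired pre-post test on all 80 participants pooled.* The standardised change is 0.25/√0.6 = 0.323, and 0.323 × √80 = 2.89. Power is again 81.4%, but there is no treatment comparison in this test.

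**2. Power of the stated contrast.** In a random-intercept model with two stages, the treatment-by-stage test is equivalent to comparing change scores.

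- SD of change = √(2(1 − 0.7)) = 0.775.
- Standard error of the difference = 0.775 × √(2/40) = 0.173.
- 0.25/0.173 = 1.44, against a critical value of about 1.96.
- Power: 30.3% (normal approximation), 29.7% (noncentral t), 29.7% (simulation, 40,000 replicates).

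A baseline-adjusted analysis would have residual SD √(1 − 0.7²) = 0.714, standard error 0.714 × √(2/40) = 0.160 and ratio 1.57. Power is 34.7% (normal) or 34.0% (noncentral t).

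**3. Summary** (noncentral t, two-sided 0.05, r = 0.7)

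| | Change score (stated model) | Baseline-adjusted |
|---|---|---|
| Power at 0.25 SD, 40 per group | 29.7% | 34.0% |
| Power at 0.25 SD, 50 per group (no loss) | 35.9% | 41.0% |
| Power at 0.50 SD, 40 per group | 81.4% | 87.1% |
| Difference with 80% power, 40 per group | 0.491 SD | 0.453 SD |
| n per group for 80% power at 0.25 SD | 152 | 130 |

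**4. Could another assumption rescue the claim?**

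- One-sided alpha gives 42% to 47% (normal approximation).
- Standardising by the SD of change instead of the SD of the score lowers power to about 20%.
- Other correlations, as change score/baseline-adjusted: 0.5 gives 19.6%/24.7%, 0.8 gives 41.5%/45.2%, 0.9 gives 69.5%/71.7%. The claim holds only at about 0.92.

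**5. The allowance for loss is correct.** 80/(1 − 0.20) = 100. It is not part of the error.

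**The case against.** The strongest defence is that the number 80 did not come from nowhere. It is what a repeated-measures power calculation returns when d is halved to f, and on that route the sample size is internally sound. This is true, but the effect that the calculation then detects is a 0.50 SD difference in change. The route would explain the figure without supporting the 0.25. It is also only a possible origin. The article names no software or convention, and the pooled pre-post test fits equally well, the more so because the section starts from a pre-to-post effect in earlier work. The error does not depend on which was used.

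A second defence is that more measurements could add power, since The intervention section says that the Brief Pain Inventory appears at the end of every visual-probe session. However, the power statement and the primary analysis use baseline and one later stage, and Table 1 lists the inventory only at baseline, evaluation and follow-up.

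Two reservations stand. The article does not mention baseline adjustment, so 34% and 0.45 SD are a favourable variant, and 30% and 0.49 SD are the figures that follow from the stated model. Also, the article does not say how a null result would be interpreted, so a misreading is a risk and not something that the plan commits to.

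**Conclusion.** The power statement is wrong as written. On the protocol's own inputs, 40 per pooled group gives 29.7% power at d = 0.25 under the stated model and 34.0% under a baseline-adjusted one, where at least 80% is claimed. The difference detectable with 80% power is 0.49 SD (0.45 SD if baseline-adjusted), which is 1.8 to 2.0 times the stated value. Retaining all 100 recruits does not close the gap.

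The conclusion rests on reading d as a between-group difference in units of the outcome SD, equal at both stages, with r = 0.7. That is the plain reading of the section, and none of the alternatives tried restores 80% for a treatment comparison of 0.25 SD. The sample size itself is not shown to be unreasonable. The effect attached to it is misstated, and this should be corrected because it is the justification for the primary outcome.

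**What to change.** Keep the sample size and restate what it can detect, for example: *With 80 evaluable participants (40 per pooled treatment group), a correlation of 0.7 between baseline and session 10 and two-sided alpha of 0.05, the trial has 80% power to detect a between-group difference in change of about 0.49 SD (about 0.45 SD if the analysis is baseline-adjusted). Power for a difference of 0.25 SD is about 30% (34% if baseline-adjusted).* Describe the effect as moderate, not small to moderate. Include the bracketed figures only if baseline adjustment is actually planned. Carry the same statement into the statistical analysis plan.

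This costs wording only. No participants are added, and the stated sensitivity becomes less favourable.

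If 0.25 SD is the difference that the sponsor really wants to detect, rewording does not repair the design. Evaluable numbers would have to rise to 2 × 152 = 304 (2 × 130 = 260 if baseline-adjusted). At 20% loss that means recruiting 304/0.8 = 380 (260/0.8 = 325) instead of 100.

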### Procedure

Interested individuals will contact the researchers on the details provided in study advertisements and will be assessed against the inclusion and exclusion criteria via telephone interview. If eligible, they will receive a copy of the participant information sheet detailing the requirements and procedure of the study, along with a link to the study website which provides further details on ABM and the research team. If the individual consents to take part, they will be required to create an online ABM account. During registration, participants will select their preferred days for training, which will be either (1) Monday/Thursday or (2) Tuesday/Friday.

Session 1 is the baseline session, and includes the first assessment visual-probe task measuring attentional biases prior to beginning the intervention, along with the questionnaire battery assessing the primary and secondary outcome measures. Randomisation will take place following session 1, where participants will be informed of the length of their training (ie, 4 or 8 weeks). Participants randomised to either of the 10-session conditions will complete four pictorial and four linguistic training sessions, while those randomised to either of the 18-session conditions will complete eight pictorial and eight linguistic training sessions (baseline and endline assessment sessions comprise the remainder of the 10/18 sessions). Participants’ attentional biases will be reassessed at endline (ie, during the final session 10/18) using the same assessment version of the visual-probe task (ie, featuring the same stimuli) used at baseline and the same questionnaire battery. Participants randomised to either of the 18-session conditions will also have their attentional biases reassessed in session 10 after their training session.

Participants’ satisfaction with the online training will also be assessed. Six months after the last session, participants will be invited to again complete the online assessment visual-probe task (same as baseline and final session 10/18) and questionnaire battery. Within 2 weeks of the completion of the 6-month follow-up session, participants will be invited to take part in a brief telephone semistructured interview including 15 questions spread across five thematic sections: (1) motivation and expectations about the study; (2) experience of the online study: person, environmental and lifestyle parameters; (3) experience of the visual-probe task; (4) understanding of the process of change; and (5) the visual-probe task as a potential therapeutic tool in pain management. The study flow is presented in table 1.

**Table 1 T1:** Schedule of enrolment, intervention and assessments

Timepoint	Study period					
	Enrolment	Postallocation				
	−*t_1_*	*t_1_* Baseline	*t_2_* Training	*t_3_* Evaluation	*t_4_* Follow-up	*t_5_* Study exit
Enrolment						
Eligibility screen	X					
Informed consent	X					
Allocation		X				
Interventions						
Attentional bias modification training			X			
Assessments						
Demographic questionnaire		X				
EOT		X	X	X	X	
BPI-SF		X		X	X	
HADS		X		X	X	
STAI		X		X	X	
MOS-SS		X		X	X	
FOP-III		X		X	X	
SOT				X		
Interview						X

*t*
_*1*_: baseline phase including standard assessment visual-probe task and questionnaires. Also includes randomisation to groups.

*t*
_*2*_: training phase including training visual-probe tasks.

*t*
_*3*_: evaluation phase including standard assessment visual-probe task and questionnaires. Participants randomised to 18-session conditions also complete evaluation phase during session 10.

*t*
_*4*_: 6-month follow-up including standard assessment visual-probe task and questionnaires.

*t*
_*5*_: telephone interview within 2 weeks of *t*
_*4*_.

BPI-SF, Brief Pain Inventory-Short Form; EOT, Engagement with the Online Training questionnaire; FOP-III, Fear of Pain Questionnaire III; HADS, Hospital Anxiety and Depression Scale; MOS-SS, Medical Outcomes Study-Sleep Scale; SOT, Satisfaction with the Online Treatment questionnaire; STAI, State-Trait Anxiety Inventory.

To retain as many participants as possible, reminder emails will be sent to participants 24 hours before each scheduled session becomes available, and also at 13:00 on the scheduled session date should the participant not have already logged into their internet-delivered ABMT (iABMT) account. An additional reminder email will be sent 1 week before their 6-month follow-up session is ready. Participants will also be sent encouragement emails informing them when they have reached specific milestones (ie, successfully completing 5 sessions for those randomised to complete 10 sessions; successfully completing 6 and 12 sessions for those randomised to 18 sessions). Participants will also have the option of receiving an SMS (short message service) on their mobile phone at 09:00 on the morning of each scheduled session.

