## Abstract

**Introduction:**

Chronic musculoskeletal pain is a complex medical condition that can significantly impact quality of life. Patients with chronic pain demonstrate attentional biases towards pain-related information. The therapeutic benefits of modifying attentional biases by implicitly training attention away from pain-related information towards neutral information have been supported in a small number of published studies. Limited research however has explored the efficacy of modifying pain-related biases via the internet. This protocol describes a randomised, double-blind, internet-delivered attentional bias modification intervention, aimed to evaluate the efficacy of the intervention on reducing pain interference. Secondary outcomes are pain intensity, state and trait anxiety, depression, pain-related fear, and sleep impairment. This study will also explore the effects of training intensity on these outcomes, along with participants’ perceptions about the therapy.

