**Methods and analysis:**

The study is a double-blind, randomised controlled trial with four arms exploring the efficacy of online attentional bias modification training versus placebo training theorised to offer no specific therapeutic benefit. Participants with chronic musculoskeletal pain will be randomised to one of four groups: (1) 10-session attentional modification group; (2) 10-session placebo training group; (3) 18-session attentional modification group; or (4) 18-session placebo training group. In the attentional modification groups, the probe-classification version of the visual-probe task will be used to implicitly train attention away from threatening information towards neutral information. Following the intervention, participants will complete a short interview exploring their perceptions about the online training. In addition, a subgroup analysis for participants aged 16–24 and 25–60 will be undertaken.

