**Trial registration number:**

NCT02232100; Pre-results.

Strengths and limitations of this studyThis protocol describes an internet-delivered intervention to explore the efficacy of attentional bias modification training in patients with chronic musculoskeletal pain.The study will recruit a diverse sample of participants in terms of age, socioeconomic status and geographical region.Results will provide important information regarding dose effects, age effects, and participants’ experiences and attitudes using the online intervention.There is limited control over the conditions under which training is completed.Independently verifying participant diagnosis is impossible.

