#### Qualitative analyses

Qualitative analysis will be used to detail participants’ experiences completing the iABMT intervention. Specifically, thematic analysis using inductive coding will be used to identify themes present in the data obtained from the semistructured interviews and the two open-ended questions included in the SOT questionnaire. Guidelines provided by Braun and Clarke^68^ will be followed. Following verbatim transcription of all interviews, initial codes will be generated. Potential themes and subthemes will then be identified from the initial coding, which subsequently will be reviewed and refined. The validity of the themes in relation to the data set will also be considered. Each theme and subtheme will then be named and defined, and a thematic map of the data finalised. Examples from the data will be illustrated for each theme and subtheme in the final report.

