### Ethics and dissemination

The study protocol was registered with ClinicalTrials.gov, with a planned start date of September 2020 and a planned end date of September 2022. All data will remain confidential and stored on password-protected systems and databases. LifeGuide and iSurvey servers both use HTTPS (hypertext transfer protocol secure) connections for security purposes. All data will be anonymised prior to dissemination, and personally identifiable information not known to anyone other than the researchers. Participants may withdraw from the intervention at any point by contacting the researchers via email or telephone, or by simply opting not to log into their iABMT account for their scheduled sessions. Participants are also encouraged to contact the researchers should they experience any distress or discomfort completing the intervention. As per university policy, any adverse events, harms or complaints arising from participation in the intervention will be reported to the University of Southampton Research Governance Office. Findings will be published in the most relevant, high-impact, peer-reviewed journals and presented at relevant conferences. Lay reports will be written for interested pain charities and patient support groups.

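### Satisfaction is scheduled only at evaluation and the interview only after the 6-month session, so the findings on perceptions will mainly reflect participants who stay

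*Protocol article*

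**What the plan says.** Perceptions are a stated aim. The abstract's introduction says: "This study will also explore the effects of training intensity on these outcomes, along with participants’ perceptions about the therapy". The strengths and limitations box promises information on participants' "experiences and attitudes using the online intervention". The Introduction and Outcome measures list engagement with, and satisfaction with, the training among the secondary outcomes, measured by the SOT and the Engagement with the Online Training questionnaire (EOT).

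The timing is as follows.

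- **Interview.** Procedure: "Within 2 weeks of the completion of the 6-month follow-up session, participants will be invited to take part in a brief telephone semistructured interview". Table 1 places it at t5, study exit. The follow-up session itself is dated from the end of training: "Six months after the last session, participants will be invited to again complete the online assessment visual-probe task".
- **SOT.** Table 1 marks it at t3 (evaluation) and nowhere else. The t3 footnote adds: "Participants randomised to 18-session conditions also complete evaluation phase during session 10".
- **EOT.** Table 1 marks it from t1 to t4, and the section on the intervention places it at the end of each visual-probe session.

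Under Qualitative analyses, "thematic analysis using inductive coding will be used to identify themes present in the data obtained from the semistructured interviews", together with the two open-ended SOT questions. No other source is named. Under Ethics and dissemination, participants may leave by contacting the researchers "or by simply opting not to log into their iABMT account for their scheduled sessions". No questionnaire or interview on leaving is described.

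**The concern.** Both sources for the themes come late. The SOT comes at the end of training (possibly also at session 10 in the 18-session arms), and the interview invitation comes after the 6-month session. A person who stops logging in at session 4, say, has left before either. People who find a repetitive online task tedious or unhelpful are plausibly over-represented among those who stop, so the views most useful for judging remote training are the ones least likely to be collected.

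Two outputs are exposed. The first is the thematic account of experiences, which may lack reasons for stopping. The second is the endline satisfaction score, above all when compared by number of sessions. That score requires staying to session 10 in one pair of arms and to session 18 in the other, so retention is mixed with dose.

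**Working it through.** **Step 1. Who supplies each source, on the text as written.**

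| Participant | EOT | SOT | Interview |
|---|---|---|---|
| Stops before session 10, does not complete the 6-month session | up to the last session attended | none | none |
| Stops before session 10, completes the 6-month session | as above, plus follow-up | none | invited |
| 18-session arm, stops between sessions 10 and 18 | up to the last session attended | possibly at session 10 | only if the 6-month session is completed |
| Completes training and follow-up | all sessions | yes | invited |

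The second row is possible but not clearly provided for. Follow-up is dated from the last session, and Procedure speaks of the final session as 10/18. It does not say when follow-up falls due for someone who never reaches that session.

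The "possibly" in the third row reflects an ambiguity. The t3 footnote suggests that the 18-session arms repeat the evaluation phase at session 10. Outcome measures, however, leaves the SOT and EOT out of its list of what is given at that point, and Procedure mentions only attentional bias there.

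**Step 2. The plan's own loss figure.** Randomisation and sample size asks for 40 per treatment group, 80 in total, allows 20% for loss, and recruits at least 100.

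80 / (1 − 0.20) = 100, which reproduces the target.

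At that allowance 100 × 0.20 = 20 people are lost and 80 could be invited to interview. The article gives no separate figure for loss by 6 months. Over an assumed range of 10% to 50%, between 100 × 0.90 = 90 and 100 × 0.50 = 50 people remain eligible for interview.

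**Step 3. How far a satisfaction figure could move.** With a proportion p lost, and dissatisfaction rates a among stayers and b among stoppers:

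- reported rate = a
- rate among all randomised = (1 − p)a + pb
- difference = p(b − a)

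The article gives neither a nor b. As an illustration, take a = 0.20 and b = 0.70 (both assumed):

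- p = 0.20: 0.8 × 0.20 + 0.2 × 0.70 = 0.30, against 0.20 reported
- p = 0.40: 0.6 × 0.20 + 0.4 × 0.70 = 0.40, against 0.20 reported

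If b = a the difference is zero, and if b < a its sign reverses. If p differs between the 10- and 18-session arms, the comparison by number of sessions shifts by the difference in p(b − a).

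**Step 4. Recall.** The interview falls at least 6 months after the last session. On the stated 4- and 8-week training periods, that is about 7 months (10-session arms) or 8 months (18-session arms) after the start. Three of its five topic areas concern motivation and expectations, the circumstances of use, and the task itself.

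**The case against.** The strongest reply has four parts.

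- **Stoppers are not silent.** The EOT is given at every session and shares the engagement and satisfaction outcome with the SOT, so someone who leaves at session 4 has answered it up to then. This stands and limits the point. Its content is in a supplement not seen here, and it is not a named source for the themes, so the gap in the qualitative account remains.
- **The missing-data plan covers secondary outcomes.** Quantitative analyses applies multiple imputation, with group-dependent shifts of the imputed values, to secondary as well as primary outcomes. This stands in part for the satisfaction score, although the SOT has no baseline value to inform the imputation. It cannot recover interview themes or open-ended answers.
- **The 18-session arms may answer the SOT at session 10.** If so, there is a comparison at equal exposure, and some later stoppers are heard. This does not help anyone who stops before session 10.
- **Interviewing at study exit is defensible.** A researcher's call about how the training works, made before the 6-month outcomes, adds contact and a possible route to unblinding before data that enter the 2×2×3 analysis. This stands. It is a good reason not to move all interviews to the end of training.

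A reader might also see a contradiction with the abstract, which says: "Following the intervention, participants will complete a short interview exploring their perceptions about the online training". That wording is less specific than Procedure, but 6 months later is still after the intervention, so the two do not conflict.

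**Conclusion.** The point holds as a selection problem in the perceptions aim and in endline satisfaction by number of sessions. It is worth fixing because the remedy is cheap. Efficacy conclusions on pain interference and the other clinical scales are unaffected.

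At the plan's own allowance, about 20 of 100 participants would supply neither an SOT answer nor an interview. This assumes that those lost leave before their first SOT and do not complete the 6-month session.

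Three stronger readings are tempting, and the article does not support them:

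- **That at least 20 go unheard.** The 20% is a planning allowance, not a floor, and actual loss could be smaller or larger.
- **That satisfaction is certainly biased upward.** This is the likely direction, but it depends on stoppers being less satisfied, on which the article has no data. The 30% and 40% figures above follow only from assumed rates.
- **That every early stopper is excluded from interview.** Someone who stops training but completes the 6-month session would be invited.

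**What to change.** 1. Trigger the existing SOT, with its two open-ended questions, automatically for every randomised participant when training ends or lapses. The team must define a lapse. LifeGuide already tracks adherence, and automatic reminder emails are already planned.
2. Keep the interview at study exit (t5), but invite participants whether or not they completed training or the 6-month session. Reserve some of the planned places for early stoppers. State when the invitation falls due for someone who never reached the final session.
3. State whether the SOT is given at session 10 in the 18-session arms.
4. Report satisfaction and themes separately for completers and stoppers.

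The cost is one automated link, a wider invitation rule and a split in reporting. Reserving places among those already planned need not add interviews. Some stoppers will not reply, so selection is reduced rather than removed, and the recall delay in the interview remains. That delay is the price of keeping researcher contact after the 6-month outcomes.
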